## Abstract

**Study design:**

Protocol for a multi-centre randomised controlled trial (the SCI-MT trial).

**Objectives:**

To determine whether 10 weeks of intensive motor training enhances neurological recovery in people with recent spinal cord injury (SCI).

**Setting:**

Fifteen spinal injury units in Australia, Scotland, England, Italy, Netherlands, Norway, and Belgium.

**Methods:**

A pragmatic randomised controlled trial will be undertaken. Two hundred and twenty people with recent SCI (onset in the preceding 10 weeks, American Spinal Injuries Association Impairment Scale (AIS) A lesion with motor function more than three levels below the motor level on one or both sides, or an AIS C or D lesion) will be randomised to receive either usual care plus intensive motor training (12 h of motor training per week for 10 weeks) or usual care alone. The primary outcome is neurological recovery at 10 weeks, measured with the Total Motor Score from the International Standards for Neurological Classification of SCI. Secondary outcomes include global measures of motor function, ability to walk, quality of life, participants’ perceptions about ability to perform self-selected goals, length of hospital stay and participants’ impressions of therapeutic benefit at 10 weeks and 6 months. A cost-effectiveness study and process evaluation will be run alongside the trial. The first participant was randomised in June 2021 and the trial is due for completion in 2025.

**Conclusions:**

The findings of the SCI-MT Trial will guide recommendations about the type and dose of inpatient therapy that optimises neurological recovery in people with SCI.

**Trial registration:**

ACTRN12621000091808 (1.2.2021).

## Introduction

Any neurological recovery following spinal cord injury (SCI) can improve mobility, independence and quality of life for people with SCI. Recovery of motor function is particularly important. This is most commonly quantified by changes in the total motor score that forms part of the International Standards for Neurological Classification of SCI [1–4]. Many different physical rehabilitation interventions and approaches have been developed and advocated over the years in an effort to promote neurological recovery and improve total motor scores [5, 6]. However, to date, no clinical trial has examined the effect of an intensive individualised programme of task-specific training supplemented with strength training provided soon after injury. We refer to this intervention as—“motor training” directed at and below the level of injury.

Task-specific training was probably first advocated in a rehabilitation context by Carr and Shepherd in the 1980s [6]. They proposed the use of task-specific training for rehabilitation after stroke. However, it has also been used in the rehabilitation of people with SCI since this time [7, 8]. Task-specific training involves the training of any functional activity such as sitting, moving from sitting to standing, standing and walking, as well as grasping and manipulating objects with the hands [9]. It relies on therapists using clinical reasoning to identify deviations from normal movement patterns and then designing individualised training programmes that typically consists of part- and whole-practice. Key features of task-specific training include goal setting, feedback and progression with an emphasis on repetitious practice [10–13]. It can be augmented with the judicious use of biofeedback, electrical stimulation, robotics and computer game-based therapy but the use of technology alone does not define it. Importantly, task-specific training does not include passive therapies such as manual therapy, vibration, joint mobilisations, passive standing, massage or stretching.

Dosage is a key consideration for any therapy for all types of neurological conditions but particularly for task-specific training where repetitious practice is at its core [11, 12, 14–17], and particularly if trying to prompt an injured spinal cord to repair itself. The need to increase the intensity of therapy was initially highlighted in 1990s by the work of Kwakkel but in the area of stroke rehabilitation where the focus is on prompting recovery of the damaged brain [18]. However, the principles and key learnings are the same [19], and the need to increase the opportunity for practice has in part lead to the evolution of interventions such as treadmill training and robotics [20]. They all provide a way of increasing repetitious practice. Yet surprisingly, the clinical trials involving people with SCI that have included measures of neurological recovery (i.e., strength of neurologically-weak muscles) have not provided therapy in particularly high dosages. For example, our own systematic review that identified 26 clinical trials [21] found that treatments ranged from 0.5 to 3 h, 3 times per week (mostly for 4–6 weeks although for 24 weeks in one trial). Similarly, observational studies suggest that people undergoing rehabilitation following SCI have limited opportunity for repetitious practice. For example, an observational study from Canada in people with SCI undergoing rehabilitation found that people with tetraplegia only performed a median of 42 attempts at moving their upper limbs each day during both physiotherapy and occupational therapy at the time of admission to rehabilitation [22]. This dropped to 15 by the time of discharge. The situation was similar for the lower limbs in all patients. This same study indicated that people received a total of 1.5 h of physiotherapy and occupational therapy a day but less than 1 h of this time was devoted to moving the upper or lower limbs in any way. A similar comprehensive study involving SCI units from Norway, Australia and Netherlands painted a similar situation with patients receiving a median of 3.8 to 5 h of therapy per week at the SCI units in the three countries [23, 24]. It is not clear how much of this time was devoted to repetitious practice and repeated attempts at movement but it would have been considerably less than 3.8 to 5 h per week because the time captured included all aspects of therapy including education, assessment, and wheelchair skill training. These findings are not unique to SCI rehabilitation. Very similar observations have been made in stroke units around the world [25, 26]. Of course the situation is changing both with stroke and spinal cord injuries, and there are many initiatives to increase therapy time and the opportunities for task-specific practice [27, 28]. However, the effectiveness of these initiatives for people with SCI is yet to be proven in a high-quality clinical trial; the motivation for the SCI-MT Trial. The SCI-MT trial attempts to provide people with as much task-specific training on top of usual therapy that it is conceivably possible soon after injury, namely 12 h per week for 10 weeks commencing within 10 weeks of injury. The task-specific training will be supplemented with strength training because clinical trials involving people with SCI point to its effectiveness [21, 29–31], and because strength is core to any attempts at movement [32, 33]. The SCI-MT Trial includes people with some preserved motor function below the motor level (for those with an American Spinal Injuries Association Impairment Scale (AIS) A lesions) or with motor incomplete lesions (AIS C and AIS D). These individuals are being targeted because they are most likely to respond to the intervention [19].

In all, the aim of the Early and Intensive Motor Training for SCI trial (SCI-MT trial) is to determine the effect of early and intensive motor training on neurological recovery of people with SCI. Secondary aims are to determine the effects of this intervention on function, ability to walk, quality of life, participants’ perceptions about ability to perform self-selected goals, length of hospital stay and participants’ impressions of therapeutic benefit. A cost-effectiveness analysis and process evaluation will be run alongside the trial. This paper describes the protocol of the SCI-MT Trial.

## Methods

### Design

An international, multi-centre, investigator-initiated, pragmatic, randomised controlled trial will be undertaken. The first participant was randomised on 7th June 2021 and the trial is due for completion in 2025. The protocol was prospectively registered with the Australian New Zealand Clinical Trials Registry (ACTRN12621000091808).

### Participants

Two hundred and twenty participants will be recruited from 15 hospitals across Australia (7 sites), Scotland (1 site), Italy (1 site), England (1 site), Norway (1 site), Netherlands (2 sites) and Belgium (2 sites). The primary eligibility criterion is an American Spinal Injuries Association Impairment Scale (AIS) A lesion with motor function more than three levels below the motor level on one or both sides, or an AIS C or D lesion, sustained in the preceding 10 weeks. Participants will only be eligible if they are likely to remain an inpatient at the hospital for 10 weeks. The full inclusion and exclusion criteria are provided in Table 1.

**Table 1 Tab1:** Inclusion and exclusion criteria for the SCI-MT trial.

Inclusion criteria	Exclusion criteria
1. Have sustained a traumatic or non-traumatic SCI of any neurological level in the preceding 10 weeks. 2. Have an AIS A lesion with motor function more than three levels below the motor level (on one or both sides), or an AIS C or AIS D lesion (as defined by the International Standards for the Neurological Classification of SCI). 3. Are male or female, over the age of 16 years at the time of signing informed consent (additional consent from a parent or guardian will be attained for those aged under 18 years).^a^ 4. Have been cleared by the medical team to commence rehabilitation (as documented in the participant’s medical files). 5. Are likely to remain an inpatient for the next 10 weeks. 6. Understand and voluntarily sign an informed consent form prior to any study related assessments/procedures being conducted. 7. Are willing and able to adhere to the study visit schedule and other protocol requirements.	1. Have any significant medical or physical condition (including pregnancy) or psychiatric illness that could prevent the person from participating in the trial, or would place the person at an unacceptable risk if he/she were to participate. 2. Are unable to provide informed consent. 3. Are family members of the research staff. 4. Are participating in another clinical trial that involves motor training of the key muscles (as defined by the International Standards for Neurological Classification of SCI). 5. Do not speak the national language.

^a^Two sites in Europe will not include 16 or 17 years olds because of regulations around the inclusion of people this age.

### Assignment of intervention

A blocked randomisation schedule stratified by site and severity of injury (paraplegia or tetraplegia) that incorporates random permuted blocks has been computer-generated by an investigator who is not involved in the day-to-day running of the trial. The schedule was uploaded onto REDCap with strict control of user rights to ensure concealment from potential participants, trial staff and investigators.

Randomisation will occur after consent has been given and the baseline assessment has been completed. The assessor will send an email request for allocation, whereupon a researcher who is otherwise not involved in the trial will log into the REDCap database, triggering the randomisation and sending of an automated email notification to the participant’s site. Allocation will be to one of two groups: a Motor Training Group or a Usual Care Group. Both groups will continue to receive usual physiotherapy and rehabilitation.

### Interventions

#### Usual care

In keeping with the pragmatic orientation of the trial, both groups will receive the physiotherapy and occupational therapy typically provided to inpatients at the site [24]. It is anticipated that for most sites this will be 3 to 6 sessions per week of both occupational therapy and physiotherapy. Some sites may also provide group classes, hydrotherapy and sessions with exercise physiologists. At some sites, usual care could include some components of the motor training intervention.

The amount and type of usual care at each site will be recorded. Specifically, the following variables will be collected: the date, time and length of both scheduled and delivered physiotherapy and occupational therapy sessions. We will differentiate scheduled and delivered sessions because scheduled sessions are often missed due to illness, medical appointments and other reasons. In addition, the time spent on seven broad types of commonly administered therapies [34] will be collected using the International SCI Physical Therapy-Occupational Therapy Basic Data Set [4].

#### Motor training

Participants allocated to the Motor Training Group will receive, in addition to usual care, an extra 12 h of motor training each week for 10 weeks. This will commence within two business days of randomisation. The 12 h per week of motor training can be provided at any time although it is anticipated that most sites will administer the additional motor training over five 2-h sessions on each weekday of the week. Some sites may provide the training in longer sessions on Saturdays and Sundays, or both. The therapy involves active, targeted motor training of neurologically-weak muscles below the level of the injury, and may consist of practice of functional activities using the principles of task-specific training, or isolated muscle contractions directed at improving strength or motor control. For example, a participant with some motor activity in the lower limbs will receive intensive task-specific training focusing on regaining the ability to sit, stand and walk. This could involve task-specific training of sitting, standing, gait training on a treadmill with bodyweight support or the use of robotic gait devices. A participant with some motor activity in the upper limbs and hands will receive intensive training of a range of reaching and grasping tasks. Training will be supplemented, where available and at the therapist’s discretion, with biofeedback, electrical stimulation, mental imagery and somatosensory stimulation. Robotics and computer game-based therapy will be used where available and appropriate provided they encourage active contraction of neurologically-weak muscles. Importantly, treatments will be individualised to the needs of each participant and follow key principles of task-specific training and strength training as outlined in a detailed intervention manual compiled for the trial. All training will address a participant’s specific motor problems. Details of the motor training provided to participants will be recorded with the same forms used to document usual care.

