#### Secondary outcomes

The effect of the intervention on upper and lower limb strength, sensation, independence, ability to walk, quality of life, perceptions of the ability to perform self-selected goals, and impressions of therapeutic benefit will be estimated using the same statistical model used in the primary analysis. For outcomes measured at both 10 weeks and 6 months, both visits will be included in the model and correlations between repeated measures will be modelled by including a random patient intercept and the effect of the intervention will be estimated at each visit by a fixed term for visit together with its interaction with the intervention.

Similar models will be used to estimate the effect of the intervention on participants’ impressions of therapeutic benefit. However, as baseline values are not collected for this outcome variable, baseline Total Motor Score will be used in the model as a pre-randomisation covariate.

The effect of the intervention on time to discharge will be estimated from a Cox model that includes baseline Total Motor Score and the stratification variables (severity as a fixed effect and site as a random effect). Patients will be censored at 6 months or when they were last known to be in hospital, whichever occurs earlier.

The effect of the intervention on type of SCI (AIS grade—5 levels) will be estimated using an ordinal logistic regression model that includes baseline AIS grade and the stratification variables. The effect of the the intervention will be estimated as the odds ratio corresponding to the odds of shifting to a worse grade category.

No subgroup, adjusted or imputed analyses are planned for any of the secondary outcomes.

If there is more than 20% non-adherence (defined as less than 80 h of additional motor training), methods of causal inference will be used to estimate the effects of intervention in the principal stratum of people who would comply with both assigned and (counterfactual) unassigned interventions [49]. Modern methods of causal mediation analysis will also be used to determine the extent to which the effects of the intervention are mediated by time spent in training [50, 51].

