## Discussion

The SCI-MT Trial when completed will be one of the largest non-pharmaceutical investigator driven trials of a rehabilitation intervention in people with recent SCI. If the intervention is found to be effective, the results will be of immediate and direct relevance for inpatient care. However, the future potential rollout of the intervention will rely on the cost as well as overcoming any real or perceived barriers. For this reason, a detailed economic analysis and process evaluation will run alongside the trial.

The SCI-MT Trial is pragmatic. Consequently, it aims to mimic how intensive motor training would be administered in the real world. Some participants may not receive the full additional 12 h per week of motor training for 10 weeks for reasons outside their and our control. The reasons for departures from the scheduled intervention will be carefully recorded and accepted as part of the real-world situation and treatment paradigm for our primary intention-to-treat analysis. This is in keeping with the standard approach for pragmatic trials [54–58]. While the trial is pragmatic, we will nonetheless use contemporary causal modelling approaches to estimate the Complier Average Causal Effect of the intervention (as described in the “Methods” section).

We anticipate some variability in usual care. This will not confound estimates of the effect of the intervention. However, time spent in training may mediate the treatment effect [51]. For this reason we will determine the extent to which the effects of the intervention are mediated by time spent in training.

As of June 2023, 128 participants have been randomised (with 7 participants randomised per month). If the current rate of recruitment continues, the trial will be fully recruited by the end of 2024, as planned. Nonetheless, one of the biggest barriers to the success of any trial is recruitment [59]. In anticipation of this problem, the trial involves many sites around the world. Each site is required to recruit between 5 and 11 participants per year. This is considered achievable. If the rate of recruitment per month drops for any reason, we will consider opening more sites.

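### The session pattern expected at most sites adds up to 10 h of motor training per week, not the 12 h per week that defines the intervention

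*Protocol article*

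**What the plan says.** The Motor training section (Methods, Interventions) gives the Motor Training Group, on top of usual care, "an extra 12 h of motor training each week for 10 weeks". The same weekly figure appears in the abstract, in the Introduction ("namely 12 h per week for 10 weeks commencing within 10 weeks of injury") and in the Discussion ("Some participants may not receive the full additional 12 h per week of motor training for 10 weeks").

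The Motor training section then turns to delivery. It says that the weekly hours may be given at any time, but that it is anticipated that "most sites will administer the additional motor training over five 2-h sessions on each weekday of the week". The next sentence adds: "Some sites may provide the training in longer sessions on Saturdays and Sundays, or both".

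A third figure stands in the Secondary outcomes part of the Data analysis section, where non-adherence is "defined as less than 80 h of additional motor training". If there is more than 20% non-adherence, a principal-stratum (complier) analysis follows. No planned total is named as the reference for the 80 h.

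**The concern.** The delivery sentence is meant to show how the stated weekly hours will be provided, but its own figures do not add up to them. The section therefore supports two planned totals.

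This matters because dose is part of the research question. The abstract's conclusion says that the findings will guide recommendations on the type and dose of inpatient therapy, and the Introduction builds the rationale on intensity. If a site scheduled the anticipated pattern, its participants would fall below the stated dose before any session was missed. The Discussion expects some shortfall, but for reasons outside the control of participants and investigators. A shortfall built into the timetable is of a different kind, and the two could be mixed in the report. An effect, or the lack of one, would then be attributed to 12 h per week when less had been planned at the sites concerned.

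**Working it through.** **Inputs**
- Stated dose: 12 h per week for 10 weeks (abstract, Introduction, Motor training, Discussion).
- Anticipated pattern at most sites: five sessions of 2 h, on weekdays (Motor training).
- Adherence cut-off: 80 h (Secondary outcomes).

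**Step 1. Planned total from the stated dose.**
12 h × 10 weeks = 120 h.

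**Step 2. Planned total from the anticipated pattern.**
5 sessions × 2 h = 10 h per week; 10 h × 10 weeks = 100 h.
The 12 h per week is not reproduced.

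**Step 3. Size of the gap.**
12 − 10 = 2 h per week, and 120 − 100 = 20 h in all.
20/120 = 16.7% below the stated dose, so full attendance gives 100/120 = 83.3% of it.

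**Step 4. Other readings of the text.**
- Taken literally, five 2-h sessions on each of five weekdays is 5 × 5 × 2 = 50 h per week. This is implausible, and it is not 12 h either.
- Weekend sessions as a supplement: the text would have to give 2 h at the weekend to every site that uses the weekday pattern. It speaks of some sites only, gives no hours, and does not say whether weekend sessions add to the weekday sessions or replace them.

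No reading of the text gives 12 h.

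**Step 5. What the 80 h cut-off means under each total.**

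| Planned total | 80 h as a share | Hours that can be missed while still adherent |
|---|---|---|
| 120 h | 80/120 = 66.7% | 120 − 80 = 40 h |
| 100 h | 80/100 = 80.0% | 100 − 80 = 20 h |

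Who counts as adherent is the same in both rows. Only the description of how demanding the cut-off is changes.

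**The case against.** The strongest reply is that the prescribed dose is consistent: 12 h per week stands in four places, and a single hedged sentence about logistics is off. The article condenses a full protocol and refers to a detailed intervention manual, neither of which is shown. The likeliest explanation is a slip in that sentence. The form of the data collection also protects the report, since the length of scheduled and delivered sessions is recorded for usual care, the same forms are used for motor training, and a mediation analysis by training time is planned. The primary intention-to-treat model and the sample size calculation use neither the session count nor the 80 h cut-off.

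Most of this stands, and it limits the seriousness of the point. It does not remove the contradiction, because nothing in the article reconciles 10 h with 12 h, and the sentence describes what is expected at most sites.

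Three stronger inferences are tempting, and the documents do not support them.
- *That 80 h shows a 100 h plan, so the three figures cannot share one total.* This assumes an 80% rule that is stated nowhere. The cut-off is given in hours alone and is compatible with either total. The 20% in that sentence reads most naturally as a share of participants, not of hours.
- *That participants between 80 h and 95 h change class with the intended total.* They do not. Under the written rule, anyone at 80 h or more is adherent. A boundary at 0.8 × 120 = 96 h would have to be supplied by the reader.
- *That sites are in fact scheduling 10 h.* The article gives a forecast, not site timetables, so this cannot be known from it.

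**Conclusion.** The Motor training section contradicts itself. The stated dose is 120 h over 10 weeks, while the pattern anticipated at most sites gives 100 h, which is 20 h or 17% lower with full attendance. This rests on reading the pattern as one 2-h session on each of five weekdays, the only plausible reading.

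The consequence is confined to how the tested intervention is described and how conclusions about dose are drawn. The definition and the trigger of the complier analysis work as written; what is open is whether 80 h should be described as 67% or 80% of the planned dose. The primary analysis and the sample size are unaffected. The point should be corrected, but it does not threaten the trial's main inference. Which figure is intended is for the investigators to say.

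**What to change.** 1. Reconcile the anticipated session pattern with the stated weekly total, so that the Motor training section agrees with itself and with the abstract, Introduction and Discussion.
2. Check that site scheduling matches the reconciled figure, and tell sites if it does not.
3. Report scheduled and delivered hours by arm next to the primary result, so that statements about dose rest on what was delivered and shortfalls in scheduling can be told apart from missed sessions.
4. When the complier analysis is interpreted, state what share of the reconciled planned total 80 h represents. The cut-off need not change for this.

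The cost is small: a clarification of wording, a check with the sites, and a line in the reporting plan. No new data are needed, because session times are already recorded.
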